# Randomised controlled trial of Interpersonal and Social Rhythm Therapy and group-based Cognitive Remediation versus Interpersonal and Social Rhythm Therapy alone for mood disorders: study protocol

**DOI:** 10.1186/s12888-022-03747-z

**Published:** 2022-02-14

**Keywords:** Bipolar Disorder, Major Depressive Disorder, Cognitive remediation, Psychotherapy, Randomised Controlled Trial, Cognitive impairment, Trial protocol

## Abstract

**Background:**

Individuals with mood disorders frequently experience cognitive impairment, which impacts on the long-term trajectory of the disorders, including being associated with persisting difficulties in occupational and psychosocial functioning, residual mood symptoms, and relapse. Current first-line treatments for mood disorders do little to improve cognitive function. Targeting cognition in clinical research is thus considered a priority. This protocol outlines a prospectively-registered randomised controlled trial (RCT) which examines the impact of adding group-based Cognitive Remediation (CR) to Interpersonal and Social Rhythm Therapy (IPSRT-CR) for individuals with mood disorders.

**Methods:**

This is a pragmatic, two-arm, single-blinded RCT comparing IPSRT-CR with IPSRT alone for adults (*n* = 100) with mood disorders (Major Depressive Disorder or Bipolar Disorder) with subjective cognitive difficulties, on discharge from Specialist Mental Health Services in Christchurch, New Zealand. Both treatment arms will receive a 12-month course of individual IPSRT (full dose = 24 sessions). At 6 months, randomisation to receive, or not, an 8-week group-based CR programme (Action-based Cognitive Remediation – New Zealand) will occur. The primary outcome will be change in Global Cognition between 6 and 12 months (treatment-end) in IPSRT-CR versus IPSRT alone. Secondary outcomes will be change in cognitive, functional, and mood outcomes at 6, 12, 18, and 24 months from baseline and exploratory outcomes include change in quality of life, medication adherence, rumination, and inflammatory markers between treatment arms. Outcome analyses will use an intention-to-treat approach. Sub-group analyses will assess the impact of baseline features on CR treatment response. Participants’ experiences of their mood disorder, including treatment, will be examined using qualitative analysis.

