### Development of the current trial

We have recently completed a pragmatic RCT [30] which examined a novel combination of CR, IPSRT and medication management for people with mood disorders. Individuals (*n* = 68) recently discharged from SMHS in Christchurch, New Zealand, were recruited into the trial and randomised to receive a 12-month course of IPSRT either with (IPSRT-CR) or without CR (IPSRT alone). For those randomised to IPSRT-CR, CR was incorporated into the 50-min therapy sessions from an early stage of treatment and continued for 12 sessions. However, the addition of CR to IPSRT did not significantly improve the primary outcome, Global Cognition, more than IPSRT alone. On the other hand, significantly greater improvement in psychosocial functioning and longitudinal depression symptoms was evident in the IPSRT group compared with the IPSRT-CR over the treatment period. During the trial, therapists had concerns about integrating CR into IPSRT at such an early stage of treatment. At study intake, 43% of the sample were ‘in episode’, and thus, therapists often prioritised stabilisation of mood over CR. This was a factor contributing to the comparatively low dose of CR (average of 7 h) provided in our trial compared with other recent RCTs of CR in BD [21, 22]. We therefore propose a follow-on RCT which will once again aim to optimise psychological treatment to improve cognitive function, and thereby, to improve functioning and mood outcomes in individuals with mood disorders. However, the CR component will, in this trial, be conducted at a later stage of treatment and will be delivered separately from ongoing IPSRT. For the first 6 months of the 12-month intervention period, all individuals will receive the same intervention; individual IPSRT. At 6 months, individuals will be randomised to receive additional group-based CR (8 sessions over 8 weeks) or no additional treatment. Shifting to a group approach should allow for a higher and more consistent dose of CR to be delivered, and at a point when individuals should have a more stable mood.

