### Randomisation

Randomisation to the group-based CR intervention, or not, will occur at 6 months. This time-point has been chosen to avoid differential early dropout based on randomisation and to provide a period of mood stabilising treatment prior to CR treatment. Computerised permuted block randomisation will be undertaken by the team’s biostatistician (CF) prior to the commencement of the study and will be stratified according to mood disorder type (BD or MDD). Sequentially numbered envelopes will be stored in a locked cabinet by an independent research coordinator and given to therapists after the 6-month research assessment. Each patient will be allocated a randomisation number which will not be re-allocated if the patient drops out of the study.

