### Procedure

Patients will enter the study within 3 months of discharge from SMHS. After study entry, individuals will be assigned a psychiatrist for ongoing medication management and a therapist who will deliver IPSRT over 12 months. Baseline assessment will occur within one week of study entry, and will involve SCID-5-RV [44] administered by a research nurse to confirm mood disorder diagnosis and comorbidities, and self-report questionnaires assessing subjective cognitive function (Cognitive Complaints in Bipolar Disorder Rating Assessment, COBRA [50]), psychosocial functioning (Social Adjustment Scale, SAS [51]), depression symptoms (Quick Inventory for Depressive Symptomatology – Self Report, QIDS-SR [52]) and other key factors described below. A research assistant, blinded to randomisation, will conduct objective cognitive assessment (described below) and assess verbal IQ (National Adult Reading Test, NART [53]) in person, as well as measures of longitudinal mood symptoms (Longitudinal Interview Follow-up Evaluation, LIFE [54]), general functioning (Functioning Assessment Short Test, FAST [55]), and medication adherence (Medication Adherence Rating Scale, MARS [56]) via telephone, within one week of baseline assessment. The psychiatrist will complete the clinician-administered versions of the QIDS (QIDS-C [52]) and Young Mania Rating Scale (YMRS [57]) and a clinical research nurse will take blood samples for biological measures.

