At 6 months, patients will undergo a second objective cognitive and functional (University of California San Diego Performance Based Skills Assessment, Brief Version (UPSA-B) [58]) assessment (blind research assistant), a telephone interview (same measures as baseline), a psychiatrist review (same measures as baseline), and self-report questionnaires (described below). Immediately following this, patients will be randomised to the group-based CR intervention, or not. The CR intervention will be provided for an 8-week period, commenced between approximately 6 months and 9 months. At treatment-end (12 months) objective cognitive and functional assessment will be repeated, along with all research measures conducted at baseline. Qualitative interviews and treatment satisfaction questionnaires will be completed at 12-months only by a research nurse trained in qualitative methodology. The same measures conducted at the 6-month time-point will be conducted at 18-months (with the exception of the UPSA-B), and at 24 months, three measures will be conducted via telephone (LIFE, FAST, MARS). Schedule of enrolments, assessments and interventions is presented in Table 1 and a populated SPIRIT checklist is provided in Additional file 1.

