### Primary outcome

The outcome measures for the trial align with ISBD Targeting Cognition Taskforce recommendations for CR trials in BD [5]. A single composite score (Global Cognition) representing overall cognitive performance at each cognitive assessment (baseline, 6 months, 12 months, 18 months) will be calculated. Change in Global Cognition from 6 months (before randomisation to group-CR) to treatment-end (12 months) will be the primary outcome measure.

Cognitive function will be assessed with a battery of cognitive tasks designed to assess verbal learning and memory, visuospatial learning and memory, sustained attention, working memory, executive functioning, psychomotor speed and social cognition. These cognitive domains are included based on recommendations from the ISBD Targeting Cognition Taskforce [5], as well as research showing these domains to be significantly impaired in acutely-unwell patients with mood disorders [6, 59] and to be sensitive to the effects of Cognitive Remediation interventions [60]. The cognitive assessment will include the following tests:Rey Auditory-Verbal Learning Task [61]Brief Visuospatial Memory Test – Revised [62]Digit Span Forwards and Backwards [63]Trail Making Test – Part A and B [64]Delis-Kaplan Executive Function System—Fluency Battery (Category Fluency, Category Switching) [64]Digit Symbol Coding [63]Continuous Performance Test [62]Stroop Task [64]Negative Affective Priming Task [65]Reading the Mind in the Eyes Test [66]Facial Expression Recognition Test [67]

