#### Cognitive functioning

##### Objective cognition

Change in Global Cognition over all study time-points (up to 18 months) to determine durability of potential cognitive changes related to receiving group-based CR, or not. In addition, more specific analysis of cognitive function will involve determining changes in individual cognitive domains. Cognitive domains will include: (i) verbal learning and memory, (ii) visuospatial learning and memory, (iii) working memory, (iv) executive function, (v) sustained attention, and (vi) social cognition.

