#### Analysis of secondary and exploratory outcomes

To assess the effect of IPSRT-CR versus IPSRT on secondary and exploratory outcomes, general linear models will be used. These models will use treatment arm (IPSRT-CR versus IPSRT) and stratum (MDD versus BD) as fixed factors. Analyses will adopt an ITT approach.

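### Secondary outcomes are framed as change from study entry, with 6 months as an outcome visit, although arms are randomised only after the 6-month assessment

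*Protocol article*

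**What the plan says.** The abstract (Methods) defines the secondary outcomes in one sentence: "Secondary outcomes will be change in cognitive, functional, and mood outcomes at 6, 12, 18, and 24 months from baseline". The Procedure section fixes what baseline means: "Baseline assessment will occur within one week of study entry".

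Randomisation comes half a year later: "Randomisation to the group-based CR intervention, or not, will occur at 6 months". Procedure describes the 6-month assessment and then says: "Immediately following this, patients will be randomised to the group-based CR intervention, or not". Before that point there is no difference in treatment (Development of the current trial): "For the first 6 months of the 12-month intervention period, all individuals will receive the same intervention; individual IPSRT".

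The primary outcome respects this design: "Change in Global Cognition from 6 months (before randomisation to group-CR) to treatment-end (12 months) will be the primary outcome measure". The secondary cognitive outcome, in the Objective cognition section, is worded differently: "Change in Global Cognition over all study time-points (up to 18 months) to determine durability of potential cognitive changes related to receiving group-based CR". That span includes the first six months. The section on analysing secondary and exploratory outcomes says: "To assess the effect of IPSRT-CR versus IPSRT on secondary and exploratory outcomes, general linear models will be used". It names arm and diagnostic stratum as fixed factors and mentions no 6-month value, either as reference or as covariate.

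**The concern.** Between entry and 6 months there are no arms. A comparison of future arms over that interval cannot show an effect of CR, whatever it shows. If it is reported beside genuine outcomes, a reader may take a chance difference for a treatment effect, or a null result for evidence against one.

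For the later visits, an entry origin adds six months of common, non-randomised change to the randomised contrast. This is the period in which the protocol expects mood and routines to stabilise. The Discussion section on timing of assessments explains that cognition was measured at 6 months so that the CR effect could be separated from that stabilisation. It gives this reason for the primary outcome only. The same reasoning applies to mood and functioning, yet the secondary outcomes are given a different origin. At stake are the clarity and precision of the secondary and exploratory comparisons, and whether they can be read on the same scale as the primary result.

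**Working it through.** **1. Reference points side by side.**

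| Item | Origin | Section |
|---|---|---|
| Primary outcome | 6 months | Primary outcome; Analysis of primary outcome |
| Secondary outcomes, general | study entry, with 6 months as a change visit | Abstract, Methods |
| Global Cognition, secondary | every visit up to 18 months | Objective cognition |
| UPSA-B | 6 months (measured only at 6 and 12) | Objective functioning |
| Secondary hypotheses | visits named: 12, 18 and 24 months; none at 6 | Primary hypothesis |

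**2. The 6-month change.** Both measurements (entry and 6 months) precede allocation, and treatment is common. The expected arm difference is exactly 0, and each test at p < 0.05 has a 5% chance of a significant result.

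**3. The later contrasts: bias.** Randomisation at 6 months balances entry-to-6-month change in expectation. The arm difference in change from entry to 12, 18 or 24 months therefore has the same expectation as the difference in change from 6 months.

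**4. The later contrasts: precision at 12 months.** Assume equal SD at each visit and write r(a,b) for the correlation between visits a and b.

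- Change from entry: variance 2·SD²·(1 − r(0,12))
- Change from 6 months: variance 2·SD²·(1 − r(6,12))
- Ratio: (1 − r(0,12)) / (1 − r(6,12))

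The protocol gives neither correlation. As a benchmark I use its planning effect of 0.6 SD, which belongs to the primary outcome. The plan's own figure reproduces: two-sided 5% and 80% power need 44 per group by the normal approximation, and 44.6, so 45, by the t-test. Power is 80% at 45 and 84% at 50 per group. Holding the raw effect fixed and changing only the origin, d = 0.6/√ratio:

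| r(6,12) | r(0,12) | Ratio | d | Power at 45 / 50 per arm |
|---|---|---|---|---|
| 0.7 | 0.7 | 1.00 | 0.60 | 80% / 84% |
| 0.7 | 0.6 | 0.4/0.3 = 1.33 | 0.52 | 68% / 73% |
| 0.8 | 0.7 | 0.3/0.2 = 1.50 | 0.49 | 63% / 68% |
| 0.9 | 0.8 | 0.2/0.1 = 2.00 | 0.42 | 51% / 56% |

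The result depends heavily on the assumptions. Letting r(0,12) run over 0.5–0.75 and r(6,12) over 0.7–0.85 independently gives ratios from 0.25/0.30 = 0.83 to 0.50/0.15 = 3.33. A ratio below 1 needs the entry value to predict the 12-month value better than the 6-month value does.

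**5. Adjustment instead of change.** Adjusting for the 6-month value leaves variance SD²·(1 − r(6,12)²). At r(6,12) = 0.7 this is 0.51·SD². Change from 6 months has 2 × 0.3 = 0.60·SD², and change from entry with r(0,12) = 0.6 has 2 × 0.4 = 0.80·SD². Even at the corner least favourable to the 6-month value (0.70 and 0.75), adjustment gives 0.51·SD² against 2 × 0.25 = 0.50·SD² for change from entry, which is practically equal.

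**The case against.** The strongest defence is that the abstract sentence is a condensed list of visits, with baseline serving as the start of the calendar, and that exact contrasts belong in the full protocol or analysis plan. The secondary hypotheses do avoid 6 months. This stands in part: the article specifies no 6-month hypothesis test. It does not dispose of the point. Six months is still listed as a visit at which change is an outcome, the only earlier assessment is study entry, and the body text does not move the origin for the later visits.

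A second defence is that change from entry is a legitimate description of a 12-month programme and is protected by randomisation. That is right about bias.

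Three stronger readings are tempting and are not supported:

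- A reader might infer that the 12-, 18- and 24-month comparisons are biased or have inflated error rates. They do not: chance imbalance in earlier recovery is ordinary sampling error, already counted in the standard error.
- A reader might count about 14 secondary measures at 6 months and compute 1 − 0.95^14 = 0.51 for at least one spurious finding. That needs independent tests, but Global Cognition averages the domains counted beside it and the clinical scales overlap. It also presumes tests that no hypothesis sets out.
- A reader might quote a fixed loss, such as a quarter or more of the sample. Step 4 of the working shows that this depends wholly on unstated correlations and can be nil.

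Nor is it true that every secondary outcome lacks a 6-month anchor, since the UPSA-B has one.

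**Conclusion.** The point holds as a matter of outcome definition. An arm difference in entry-to-6-month change cannot reflect CR and should not be listed as an outcome of the comparison. The later contrasts from entry are valid but may be noisier than they need be. The illustration is a variance ratio of 1.33 at 12 months (power 73% instead of 84% at 50 per arm for an effect of 0.6), under assumed correlations of 0.7 and 0.6 and equal SDs. There is no loss if the correlations are equal, and nothing has been computed for 18 or 24 months.

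Only secondary and exploratory outcomes are affected; the primary outcome and the sample size stand. It is a moderate point, worth correcting because the better reference value is already collected and the protocol's own rationale calls for it.

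**What to change.** For every secondary and exploratory measure collected at 6 months, define the arm comparisons at 12, 18 and 24 months (as far as that measure is scheduled) as change from the 6-month pre-randomisation value, or as the later value adjusted for it. Adjustment is the more precise choice. The study-entry value may be added as a second covariate, but this is optional.

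Remove 6 months as a between-arm outcome visit. Report entry-to-6-month change descriptively, as the uncontrolled course under the common therapy. Bring the abstract's Methods paragraph, the Objective cognition section and the section on analysing secondary and exploratory outcomes into line with this.

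The cost is rewording, done before the data are analysed by arm. No visit, measure or participant is added, and the sample size does not change.

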**Discussion:**

This will be the first RCT to combine group-based CR with an evidence-based psychotherapy for adults with mood disorders. The trial may provide valuable information regarding how we can help promote long-term recovery from mood disorders. Many issues have been considered in developing this protocol, including: recruitment of the spectrum of mood disorders, screening for cognitive impairment, dose and timing of the CR intervention, choice of comparator treatment, and choice of outcome measures.

**Trial registration:**

Australian and New Zealand Clinical Trials Registry, ACTRN12619001080112. Registered on 6 August 2019.

**Supplementary Information:**

The online version contains supplementary material available at 10.1186/s12888-022-03747-z.

## Background

The spectrum of mood disorders includes Major Depressive Disorder (MDD) and Bipolar Disorder (BD). Mood disorders are highly recurrent, long-term conditions, and are among the leading causes of disability worldwide [1, 2]. In New Zealand, high prevalence and disability associated with mood disorders applies to all ethnic groups and causes significant interference with functioning and suffering [3]. Rates of relapse in BD for those receiving routine care (medication alone) are 43% within 12 months, 57% within 2 years, and 77% within 4 years [4]. In Christchurch (New Zealand), where care consists mainly of medication and case management, 40% of patients admitted to a Specialist Mental Health Service (SMHS) with a mood disorder were readmitted into a SMHS within a year of discharge (data from Canterbury District Health Board SMHS). Reducing relapse and achieving longer duration between episodes is important because sustained periods of recovery of between 1 and 3 years are associated with progressively lower future relapse [4]. It is thus vital for treatment research in mood disorders to examine interventions that can be used alongside medication in order to promote long-term recovery.

### Targeting cognition in mood disorder treatment trials

Cognition has been identified as an important treatment target in mood disorders in attempting to improve functioning and reduce relapse rates [5]. A substantial portion of patients with mood disorders exhibit cognitive impairment [6, 7] across a range of domains (learning and memory, attention, executive function, psychomotor speed, social cognition) [8, 9]. Cognitive impairment often persists into recovery [10], and relates to problems in occupational and psychosocial functioning [10, 11]. Aspects of cognitive impairment have also been associated with increased risk of relapse [12].

Evidence suggests that current first-line treatments for mood disorders do little to improve cognitive function. Regarding first-line medications, a large-scale randomised trial (*n * = 1008) comparing effectiveness of three common antidepressant medications (escitalopram, sertraline, venlafaxine) on cognitive outcomes showed no effect of any medication [13]. In line with this, mega-analysis using patient level data in those with euthymic BD reported no consistent effect of commonly prescribed mood stabilising or antipsychotic medications on cognitive function [14]. A recent systematic review examining evidence-based psychological therapies in mood disorders concluded there was minimal evidence of pro-cognitive effects across therapies and across diagnoses (MDD or BD) [15]. An exception was metacognitive therapy, incorporating simple cognitive training techniques (Attention Training Technique), which has shown preliminary evidence of improving aspects of cognitive function [16]. Clearly, interventions targeting cognitive function in mood disorders are required to be able to improve cognitive and functional recovery.

Cognitive Remediation (CR) is an intervention involving a combination of repetitive cognitive training, strategy coaching, transfer of cognitive skills to daily life, and techniques to overcome cognitively-challenging tasks [17]. Systematic reviews examining effectiveness of CR interventions in BD have reported preliminary pro-cognitive effects [18] or inconclusive results [19, 20]. Two recent randomised controlled trials (RCTs) in euthymic BD reported improved aspects of cognitive function, particularly executive function, following CR (10–12 weeks in duration). Strawbridge et al. [21] reported additional improvement in psychosocial functioning at treatment-end and 3-month follow-up, while Ott et al. [22] showed improvement in subjective cognitive function at treatment-end only. In MDD, meta-analysis of CR reported short-term, moderate pro-cognitive effects, and small effects on daily functioning and mood symptoms, but none of these effects were durable [23]. In comparison with CR trials in BD, MDD trials have generally been smaller, shorter in CR duration, more variable in whether CR commences in the acute or remitted phase, and have often focused on short-term symptom reduction rather than longer-term functional outcomes. Therefore, larger RCTs of CR interventions in mood disorders, examining durability of multiple outcomes, are required.

